### Participants

#### Recruitment

We are recruiting participants who receive health care from a large medical center residing in the southern United States through direct referrals from health care professionals (eg, physicians or therapists) and distribution of study materials (eg, flyers, newsletters, or advertisements) to various clinics, hospitals, and medical rehabilitation service providers.

#### Eligibility Criteria

Adult wheelchair users who do not participate in health-enhancing volumes of exercise [16] and have ≥2 cardiometabolic risk factors are recruited for this study. Potential participants are prescreened for the eligibility criteria via telephone screening, medication list review, and physical screening. The onsite, physical screening to confirm eligibility occurs in the baseline visit.

Textbox 1 lists the specific participant eligibility criteria. Participants undergo a 2-stage screening process. The first stage, eligibility screening, is undertaken during a scripted phone screening by the project coordinator. The presence of CMH risk factors [25] is initially screened based on the self-reported height and weight to estimate the BMI and waist circumference, as well as the physician-prescribed medications that are relevant to CMH risk factors (eg, are you taking any medications related to increased BP? Has your doctor ever expressed concerns about your cholesterol level?).

Inclusion and exclusion criteria.
**Inclusion criteria**
Full-time or part-time use of a wheelchair device (manual wheelchair, power wheelchair, or electric scooter) self-reported as the primary means of mobilityAged ≥18 yearsAble to use arms to exerciseObtaining <90 minutes of moderate-to-vigorous intensity exercise per week in the last month≥2 cardiometabolic risk factors:Elevated waist circumference: ≥102 cm in men and ≥88 cm in womenElevated triglycerides: ≥150 mg/dLReduced high-density lipoprotein cholesterol fraction: <40 mg/dL in men, <50 mg/dL in womenElevated blood pressure (BP): ≥130 mm Hg systolic BP or ≥85 mm Hg diastolic BPElevated fasting glucose: ≥100 mg/dLNo contraindication to participate in moderate-to-vigorous intensity exercise as informed by physician’s medical clearance for exerciseNot currently participating in a structured exercise programAble to converse and read in English
**Exclusion criteria**
Medically unstable to perform the prescribed home exercise as determined by their physicianHigh-level tetraplegia and unable to use arms to exerciseNo internet access was determined via self-report and internet speed testPositive pregnancy testOther physical conditions that can potentially prevent them from participating in an exercise routine (eg, pressure sore and open wound)
**Justification for exclusion criteria**
Exclusion of pregnant individuals: The use of dual-energy x-ray absorptiometry for body composition analysis involves minimal radiation exposure. However, to eliminate any potential risk to the fetus, pregnant individuals will be excluded.Exclusion of individuals with medical instability: To minimize the risk of adverse events during the intervention, participants must be medically stable and have clearance from a health care provider to engage in moderate-to-vigorous intensity exercise.Internet access requirement: As the intervention is delivered via a tele-exercise platform, participants must have reliable internet access to ensure they can fully engage in the program, participate in live sessions, and receive remote monitoring and feedback.

The second screening stage involves a review of participation medications (self-reported) and a physical examination by laboratory staff. The medication list is obtained before the baseline visit using a secure electronic survey, and this study’s staff reviews and verbally confirms them during the baseline visit. If the potential participants currently take ≥2 medications related to CMH risk factors, then they can proceed to the baseline physical examinations. Otherwise, they proceed to physical screening in the following order: manual BP, tape-measured waist circumference, and fingerstick blood sampling for triglycerides, high-density lipoprotein cholesterol fraction, and glucose using the lipid analyzer (Cholestech LDX, Abbott). If the potential participants meet the eligibility criteria with BP and waist circumference, fingerstick blood sampling is omitted.

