However, there is limited evidence that aerobic exercise improves CMH among wheelchair users. Most evidence is observational and nearly all randomized controlled trials (RCTs) have small sample sizes limited to a single population (eg, those with SCI). There are no large confirmatory RCTs that demonstrate that aerobic exercise improves CMH in adult wheelchair users. A recent meta-analysis of 3 RCTs, with samples of 15-21 adults with SCI, determined that 6-weeks of aerobic exercise improved CMH among adults with SCI (ie, decreased fasting glucose and insulin and increased fasting high-density lipoprotein cholesterol fraction) [11]. Another meta-analysis of 16 pre-post and controlled trials with sample sizes of 5-20 adults with SCI determined that vigorous exercise training improved cardiorespiratory fitness in adults with SCI [12] (ie, increased peak power output, muscular strength, and time to fatigue) but did not improve CMH risk factors, such as blood pressure (BP), cholesterol, and insulin sensitivity. Noted limitations of these studies included small sample sizes, inclusion of participants already within healthy ranges for CMH at baseline, lack of a control group, use of laboratory-based training, and inclusion of a single population (those with SCI). Therefore, the finding that CMH measures did not improve must be interpreted with caution.

Interventions that have sought to improve physical activity levels have also failed to improve CMH among wheelchair users. The largest physical activity trial among wheelchair users (n=128), Workout on Wheels, increased self-reported physical activity by 17 min/wk, with no significant between-group differences in cardiorespiratory fitness or CMH measures [13]. Other recent lifestyle interventions (eg, behavioral coaching) have similarly failed to elicit significant CMH benefits among people with disabilities, even while achieving large sample sizes [14]. Thus, the exercise doses or intensity studied may be suboptimal for improving CMH among people with physical disabilities. Despite failures to improve CMH, many of these physical activity trials have informed the creation of the most recent guideline related to CMH for people with SCI [15,16]. Collectively, there is an urgent need for well-designed interventions that can provide an effective exercise dose for people with disabilities, including wheelchair users, while obtaining evidence for improving CMH through physical activity.

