### Primary Outcome Measures

CMH outcomes are assessed via venipuncture blood specimen, brachial cuff BP, and body composition.

High sensitivity C-reactive protein (hsCRP; mg/L): hsCRP is a critical marker of inflammation that contributes to proinflammatory and prothrombotic elements of cardiovascular risk. A single hsCRP measure is a strong predictor of myocardial infarction or coronary heart disease mortality and several other diseases of the circulatory system in people without a history of such conditions [28]. Changes in hsCRP may occur from as early as 8 weeks of exercise [29].Hemoglobin A1c (HbA1c, mmol/mol): HbA1c is a measure of red blood cell mean hemoglobin glycation over the previous 3 months. Exercise interventions without a dietary component should yield a small to moderate effect on HbA1c after a month of training [30].Fasting insulin (μIU/mL): A high fasting insulin level indicates the presence of insulin resistance and whether an individual shows glucose intolerance. Exercise interventions without a dietary component should yield a small beneficial change in fasting insulin levels after a month of training [30].Fasting glucose (mmol/L) and homeostatic model assessment of insulin resistance: This is calculated as [fasting insulin (μU/mL) × fasting glucose (mmol/L)]/22.5 [31].Fasting triglycerides (mg/dL): A triglyceride level >150 mg/dL, is largely supported as an indicator of cardiovascular risk [32,33]. Exercise interventions without a dietary component should yield a small beneficial change in triglyceride levels after a month of training [30], even among people with normal triglyceride levels [34].Fasting cholesterol (mg/dL): Abnormalities in the lipid profile, including elevated total and LDL cholesterol as well as decreased HDL cholesterol, are predictors of future cardiovascular disease among young and middle-aged people [35,36]. Exercise interventions without a dietary component should yield a small effect after 1 month [30].BP (mmHg): Moderate-intensity exercise has been shown to reduce BP [37].Waist circumference (cm): The waist circumference is measured at the level of the superior border of the iliac crest, above the umbilical level, and at the midline level [38] using a Gulick tape.BMI (kg/m^2^): Dual-energy x-ray absorptiometry (DXA) scan is used to measure weight-adjusted BMI, in addition to total mass, lean mass, and fat mass. It is evident that people with SCI often have elevated waist circumference (≥94 cm), but their BMI is less than 30 kg/m2[39].

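### The medication route at second-stage screening bypasses the measured risk-factor check and counts drugs rather than distinct factors, so it does not implement the stated inclusion criterion

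*Protocol article*

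**What the plan says.** Textbox 1 of the protocol article (Inclusion criteria) asks for at least two cardiometabolic risk factors and defines all five by a measurement. The first reads "Elevated waist circumference: ≥102 cm in men", with a separate limit for women. The others are cut-offs for triglycerides, HDL cholesterol, blood pressure and fasting glucose. None has an alternative for people under drug treatment.

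Screening has two stages. By telephone, risk factors are "initially screened based on the self-reported height and weight to estimate the BMI and waist circumference", together with questions on prescribed medication. The second stage is described after the justification of the exclusion criteria: "The second screening stage involves a review of participation medications (self-reported) and a physical examination by laboratory staff". There the path splits. One branch is "If the potential participants currently take ≥2 medications related to CMH risk factors, then they can proceed to the baseline physical examinations". The other is "Otherwise, they proceed to physical screening in the following order: manual BP, tape-measured waist circumference, and fingerstick blood sampling".

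Other sections read as if everyone were checked. Eligibility Criteria states: "The onsite, physical screening to confirm eligibility occurs in the baseline visit". Procedure says that staff blinded to treatment carry out the second level of screening on the basis of CMH indicators. Random Assignment places randomisation after eligibility has been determined and baseline assessments are complete.

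**The concern.** The criterion and the rule that applies it differ in two ways. The rule accepts treatment in place of a measured value, which Textbox 1 does not. It also counts drugs where Textbox 1 counts risk factors. A person on two blood-pressure drugs, with controlled pressure and nothing else out of range, satisfies the screening rule and meets none of the five thresholds.

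At stake is whether the enrolled sample is the one described: wheelchair users with at least two risk factors and a poor cardiometabolic profile. In Background, the authors list "inclusion of participants already within healthy ranges for CMH at baseline" among the limitations of earlier studies, and conclude that the absence of improvement in CMH measures must be read with caution. A route that can admit similar people exposes this trial to the same criticism, to an extent that nobody could report unless the route of entry is recorded.

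**Working it through.** The point rests on comparing the text, not on a calculation.

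**1. Three rules applied to the same people.** The cases are hypothetical. Each person is assumed to meet all other criteria.

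| Case | CMH drugs | Distinct factors treated | Thresholds met when measured | Second-stage rule (≥2 drugs) | Textbox 1 (≥2 measured) | ≥2 distinct factors, treatment counted |
|---|---|---|---|---|---|---|
| A: two BP drugs, all values normal | 2 | 1 | 0 | passes | fails | fails (1) |
| B: one BP drug and one glucose drug, all values normal | 2 | 2 | 0 | passes | fails | passes (2) |
| C: two BP drugs, BP and waist still raised | 2 | 1 | 2 | passes | passes | passes (BP, waist) |
| D: one BP drug, all values normal | 1 | 1 | 0 | goes to measured check | fails | fails (1) |

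Case B turns on whether treatment counts as having the factor, which Textbox 1 does not say. Case A fails whichever way that is settled, yet the screening rule lets it through. Cases A and D have the same single treated factor and the same normal values. They are handled differently only because A takes one more drug.

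**2. The two branches count different things.** In the measured branch, fingerstick sampling is omitted once blood pressure and waist both qualify, so that branch counts distinct factors. The medication branch counts drugs.

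**3. Is the gap closed later?**
- Telephone stage: self-reported height, weight and medication. Nothing is measured.
- Medication list: self-reported, then confirmed verbally by staff.
- Baseline examinations: blood pressure, waist, triglycerides, cholesterol and glucose are primary outcomes, so the values are collected before randomisation. No section says that they are compared with the Textbox 1 limits.
- Eligibility Criteria and Procedure: both imply an onsite check based on indicators for everyone. The medication branch contradicts this unless a recheck exists that the article does not state.

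**4. Can the effect on power be sized?** The plan's own figure reproduces. A two-sided two-sample t test at the 5% level, with 50 per group and d = 0.566, has 80.0% power (noncentral t, 98 degrees of freedom). The stated differences correspond to 24.4/43 = 0.567, 2.5/4.3 = 0.581 and 12.7/22.4 = 0.567. The power section has no arithmetic error.

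A diluted effect would be d × [1 − f(1 − r)], where f is the share entering with fewer than two measured factors and r is the fraction of the full effect that they keep. The document gives neither f nor r, so any power figure would reflect only the values chosen for them.

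**The case against.** The strongest reply is that treatment is evidently meant as evidence of a risk factor. The telephone stage already uses prescribed medication to judge whether factors are present, so the likelier fault is incomplete wording in Textbox 1. This is a fair reading and may be right, but it only settles case B. Two drugs for one factor are still one factor.

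It can also be said that the rule lets people proceed to baseline examinations and does not say that they are enrolled. Eligibility must be determined before randomisation, and the relevant markers are measured at that visit. This stands in part. A reader might infer that ineligible people are certain to be randomised. The document does not show that: it neither states nor excludes a recheck.

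A reader might also infer that the trial loses a definite amount of power. That is not supported either, for four reasons beyond the unknown share:
- Primary Outcome Measures expects a triglyceride benefit "even among people with normal triglyceride levels", so zero response in such people cannot be assumed.
- Two of the three markers used for the power calculation, total cholesterol and body fat, are not among the five inclusion factors. Falling below the inclusion thresholds does not show that there is no room to improve on them.
- Any two-of-five rule admits people who are normal on a given marker. Someone qualifying on waist and blood pressure may have normal triglycerides.
- The effect size of 0.566 is a detectable difference, not an effect estimated in a risk-selected group that would then shrink.

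Finally, medication use (use versus nonuse) is a possible covariate and a candidate moderator. That helps to describe treated participants, but it does not separate those with fewer than two measured factors from treated people who still exceed the thresholds.

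**Conclusion.** The inconsistency holds on the text alone. The stated criterion is at least two measured factors. The operating rule lets people on two or more CMH-related drugs skip the measured check, it counts drugs and not factors, and no later check against the thresholds is stated. Some otherwise eligible participants could therefore enter with fewer than two risk factors.

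How many is unknown. Dilution of the effect is a possibility that cannot be quantified from this document, and no loss of power should be claimed. The verdict assumes that no unstated recheck takes place at baseline. If one does, the defect is in the wording, and the passages still need to be reconciled. The point is worth correcting, but it does not undermine the design.

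**What to change.** 1. Reconcile Eligibility Criteria, Textbox 1, the second-stage screening text and Procedure so that screening counts distinct risk factors.
2. State in Textbox 1 whether drug treatment for a factor counts as meeting it. That decision belongs to the sponsor.
3. Send anyone whose medications cover only one factor through the blood-pressure, waist and fingerstick steps that already exist.
4. Record for every participant the route of entry and the number of thresholds met at baseline. The HDL fraction is assumed to be reported with the fasting cholesterol results. Glucose is listed in mmol/L as an outcome and in mg/dL as a threshold, so one must be converted.
5. Keep everyone randomised in the intent-to-treat analysis, and add a sensitivity analysis restricted to participants with at least two measured factors at baseline. Because that subset is defined by pre-randomisation values, the comparison within it remains randomised. It also covers treated people with normal values (case B), whom a distinct-factor rule would still admit if treatment counts.

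The cost is a wording amendment, a few more fingersticks and screen failures, and one extra analysis. The restricted analysis will have fewer participants and less precision. The change is timely: 16 of 132 had been recruited by August 20, 2024, leaving 132 − 16 = 116 still to be screened at that date.

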### Ethical Considerations

Ethical approval for this study was obtained from the University of Alabama at Birmingham Institutional Review Board on December 22, 2022 (IRB-300009718). This study’s protocol adheres to all relevant ethical guidelines for research involving human participants, including medical records and patient information.

Informed consent will be obtained from all participants before the baseline visit or during the baseline visit. During the consent process, participants will receive detailed instructions about this study, including its objectives, procedures, potential benefits, and any associated risks or discomforts. They are also informed of their rights, including the ability to withdraw from this study at any time, to ensure that their participation is completely voluntary. This comprehensive approach is designed to ensure that all participants fully understand this study before providing their consent.

To protect participants’ privacy, all data collected will be anonymized by assigning each participant with a study number to ensure that no personally identifiable information is directly linked to the data. Demographic, personal, and exercise test data will be securely stored in REDCap (Research Electronic Data Capture; Vanderbilt University) and Box (Box, Inc), which are secure, password-protected databases. Access to these data will be limited to authorized research personnel, and all information obtained during this study will be used for research purposes only.

Participants will receive up to US $830 for their participation in this study. Compensation will be provided in stages, with participants receiving US $150 at the baseline assessment, US $200 at the 12-week assessment, US $250 at the 24-week assessment, and US $150 at the 36-week assessment. In addition, participants will receive US $40 for each of the two interview sessions to ensure fairness and transparency in recognition of their time and effort.

### Power Analysis and Sample Size

We plan to recruit 132 participants into this study (66 per treatment group), with the expectation that at least 100 (50 per group) will complete this study. We anticipate an attrition rate of 23% based on the average attrition rate between the largest home-based behavioral interventions among wheelchair users (33%) [13] and our scoping review of exercise trials for people with various disabilities (13%) [14]. Due to the nature of the proposed exercise training involving one-on-one training and supervision, we believe that the role of exercise training coaches in this study will lead to lower attrition rates as it has in our past studies [26].

Power calculations were performed using nQuery (version 8.5; Statsols). For the primary outcome of CMH, we obtained SDs of biomarkers of this outcome from our pilot study among individuals with SCI (6-wk arm crank exercise training), including SDs of 43 mg/dL for total cholesterol, 4.3% for body fat, and 22.4 mg/dL for triglycerides [27]. Assuming a final sample size of 50 participants per group, a 2-sided 2-group *t* test (2-tailed), and a significance level of .05, we will have at least 80% power to detect differences of 24.4 mg/dL for total cholesterol, 2.5% for body fat, and 12.7 mg/dL for triglycerides (and greater) between the intervention and control groups as being statistically significant. This is equivalent to detecting an effect size (Cohen *d*) of 0.566 (a moderate effect size) as statistically significant between the two groups.

### Outcomes

Outcomes are assessed at baseline, midintervention (12 wk), postintervention (24 wk), and follow-up (36 wk) time points. Physiological outcomes are assessed by anonymous-to-treatment assessors. The assessors are not involved in random assignment or the intervention delivery and do not directly communicate with the M2M instructors and assistant health coaches about participants. Data collection with physiological outcomes is conducted at a local research facility affiliated with a major medical center. Self-reported outcomes are administrated via a secure electronic database, referred to as REDCap. Online platform analytics are used to assess heart rate (HR) and video minutes viewed and stored in the cloud. Figure 1 shows the schedule of assessments.

**Figure 1 figure1:**
[figure not shown]
Example template of recommended content for the schedule of enrollment, interventions, and assessments. CMH: cardiometabolic health; M2M-C: movement-to-music cardiovascular; SET: standard exercise training.

### Primary Outcome Measures

CMH outcomes are assessed via venipuncture blood specimen, brachial cuff BP, and body composition.

High sensitivity C-reactive protein (hsCRP; mg/L): hsCRP is a critical marker of inflammation that contributes to proinflammatory and prothrombotic elements of cardiovascular risk. A single hsCRP measure is a strong predictor of myocardial infarction or coronary heart disease mortality and several other diseases of the circulatory system in people without a history of such conditions [28]. Changes in hsCRP may occur from as early as 8 weeks of exercise [29].Hemoglobin A1c (HbA1c, mmol/mol): HbA1c is a measure of red blood cell mean hemoglobin glycation over the previous 3 months. Exercise interventions without a dietary component should yield a small to moderate effect on HbA1c after a month of training [30].Fasting insulin (μIU/mL): A high fasting insulin level indicates the presence of insulin resistance and whether an individual shows glucose intolerance. Exercise interventions without a dietary component should yield a small beneficial change in fasting insulin levels after a month of training [30].Fasting glucose (mmol/L) and homeostatic model assessment of insulin resistance: This is calculated as [fasting insulin (μU/mL) × fasting glucose (mmol/L)]/22.5 [31].Fasting triglycerides (mg/dL): A triglyceride level >150 mg/dL, is largely supported as an indicator of cardiovascular risk [32,33]. Exercise interventions without a dietary component should yield a small beneficial change in triglyceride levels after a month of training [30], even among people with normal triglyceride levels [34].Fasting cholesterol (mg/dL): Abnormalities in the lipid profile, including elevated total and LDL cholesterol as well as decreased HDL cholesterol, are predictors of future cardiovascular disease among young and middle-aged people [35,36]. Exercise interventions without a dietary component should yield a small effect after 1 month [30].BP (mmHg): Moderate-intensity exercise has been shown to reduce BP [37].Waist circumference (cm): The waist circumference is measured at the level of the superior border of the iliac crest, above the umbilical level, and at the midline level [38] using a Gulick tape.BMI (kg/m^2^): Dual-energy x-ray absorptiometry (DXA) scan is used to measure weight-adjusted BMI, in addition to total mass, lean mass, and fat mass. It is evident that people with SCI often have elevated waist circumference (≥94 cm), but their BMI is less than 30 kg/m2[39].
